**Fig. 1 Fig1:**
[figure not shown]
Flow diagram of recruitment, randomization and assessments. FU = Follow-up

### Participants’ eligibility

Children with an ASD (DSM-IV-TR: Autistic disorder, Asperger disorder, PDD-NOS; [26]) in the age between 8 to 16 years old will be assessed for eligibility by a screening. This screening consists of filling in an anxiety questionnaire by both children (SCAS-C; [28]) and parents (SCAS-P; [29]). When children have at least subclinical levels of anxiety, they are eligible for participation in the study. Moreover, they have to have sufficient knowledge of the Dutch language. Exclusion criteria are absence of parental permission and presence of prominent suicidal ideation or other severe psychiatric problems that need immediate treatment (*e.g.* severe trauma’s).

### Procedure

Contexts of recruitment are mental health institutes (*e.g.* GGZ Oost Brabant) and special education schools in the Netherlands. First, parents will receive a letter with information about the screening and the study. Moreover, children and parents will be asked to fill in the SCAS-C/P [28, 29]. When children have at least subclinical levels of anxiety and meet the other inclusion criteria, children and parents will be approached to participate in the study. If children and parents agree with participation, active written informed consent of the parents and the children who are above the age of 12 will be obtained.

After obtaining active written informed consent, children will be randomly allocated to the experimental or control condition. Children in the experimental condition will play Mindlight individually for one hour per week during 6 consecutive weeks at the recruitment location. Moreover, children may receive treatment as usual (TAU) parallel with Mindlight. TAU will mainly be offered by mental health institutes and might for example consist of psycho-education on ASD, play/drama therapy, parent guidance and/or medication. These types of TAU will be monitored and reported during the course of the study, and will be tested as potential confounders in the analyses. Children in the control condition will play the computer game Triple Town individually for one hour per week during 6 consecutive weeks at the recruitment location. Again, children may receive TAU parallel with the game. Moreover, they will have the opportunity to play Mindlight after the 3-months follow-up if this game turns out to be effective.

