**Discussion:**

This paper aims to describe a study that will examine the effect of the serious game Mindlight on (sub) clinical anxiety symptoms of children with an ASD in the age of 8–16 years old. It is expected that children in the experimental condition will show lower levels of anxiety symptoms at 3-months follow-up, compared to children in the control condition. If Mindlight turns out to be effective, it could be an important contribution to the already existing interventions for anxiety in children with an ASD. Mindlight could then be implemented as an evidence-based treatment for anxiety symptoms in children with an ASD in mental health institutes and special education schools.

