### Data analysis/statistical analysis

Following the intention-to-treat principle [48], all children randomized to a condition will be included in the analyses to test the study objectives. Multiple imputations will be used for missing observations at post-intervention and 3-month follow-up. Reporting of the results of the study will be in accordance with the CONSORT 2010 Statement [25].

To investigate the differences in the development of anxiety symptoms between children in the experimental condition and children in the control condition, a 3 (within-subjects: pre, post, follow-up) by 2 (condition: experimental vs. control) ANOVA (repeated measures) will be conducted, with anxiety symptoms (child report) as the dependent variable. The direct effect of Mindlight on parent report of child anxiety, parent/child report of depressive symptoms, and parent/teacher report of social functioning and behavior problems will be investigated in the same way. Furthermore, remission rates of the anxiety disorders that were diagnosed at baseline (with ADIS-P) will be calculated at 3-months follow-up, and Chi-square (*χ*^2^) tests will be conducted to compare remission rates between the experimental and control group. In the above mentioned analysis plan it is assumed that the children will play the game individually and that therefore the data will not be clustered. However, in case of clustered data due to the formation of groups in which several children play the game in the same room, the analyses will be conducted in MPLUS 6.11 [49].

Finally, possible baseline differences between the two conditions in demographic variables (*e.g.* age, sex, educational level), anxiety symptoms, gaming behaviour and treatment expectancies will be checked. Moreover, possible differences in TAU between the experimental and control condition will be checked at all time points. Variables that show different distributions between the two groups will be entered as confounders in all models testing the effectiveness of the intervention.

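### Recruitment context is missing from the listed covariates, while the plan relies on imbalance-triggered adjustment that includes TAU measured after randomisation

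*Protocol article*

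**What the plan says.** The Procedure section of the protocol article names two sources of children: "Contexts of recruitment are mental health institutes" and, in the same sentence, special education schools. In both arms the game is played "during 6 consecutive weeks at the recruitment location". Children may receive TAU alongside either game, and "TAU will mainly be offered by mental health institutes". The types of TAU are to be monitored and reported, and "will be tested as potential confounders in the analyses". Allocation is described only in general terms: "children will be randomly allocated to the experimental or control condition".

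The section on data analysis sets a covariate rule. It checks "possible baseline differences between the two conditions in demographic variables", with age, sex and educational level as examples, together with anxiety symptoms, gaming behaviour and treatment expectancies. It adds that "possible differences in TAU between the experimental and control condition will be checked at all time points". Any variable whose distribution differs between the arms then enters every effectiveness model as a confounder. Recruitment context is not on the list. The wording that marks examples belongs to the demographic item alone, and the type of recruiting institution is not naturally a demographic variable.

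The main analysis is a repeated-measures ANOVA with three time points and two conditions. The abstract foresees, if the game works, that "Mindlight could then be implemented as an evidence-based treatment for anxiety symptoms in children with an ASD in mental health institutes and special education schools".

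**The concern.** The plan treats TAU as important enough to test as a confounder and says that one of its two kinds of recruitment setting mainly provides it. Setting is fixed before allocation, is known for every child and cannot be changed by the game. It can be adjusted for without risk of bias.

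The stated rule is weaker in two respects. First, a covariate enters only after an imbalance has been seen, so the data choose the model, and they choose it on imbalance and not on relevance to the outcome. Second, TAU at post-intervention and at follow-up is measured after randomisation. A child who improves may stop other care, and one who does not may start it. If the arms then differ in TAU, the difference may be a consequence of the intervention, and adjusting for it can remove part of the effect or bias it. The list thus includes the riskier variable and leaves out the safer one.

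At stake are some precision and some protection against a chance imbalance. The validity of the randomised comparison is not in question.

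**Working it through.** **The plan's own figure.** Inputs from the Sample size section: f = .25, alpha .05, power .80. With two groups, m = 3 measurements and a correlation between measurements of 0.5 (assumed; not stated), the between-factors repeated-measures calculation has noncentrality f² × N × m / (1 + (m − 1) × rho).

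- At N = 86: 0.0625 × 86 × 3 / (1 + 2 × 0.5) = 8.06, and the power is 0.801. So 86 is reproduced.
- 86 × 1.4 = 120.4, which matches 120, or 60 per arm.

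Nothing below alters these figures.

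**Chance of an imbalance in context.** The documents do not give the split between institutes and schools, so the range 50-70% from institutes is assumed, as is allocation that ignores context. With K institute children among 120 and 60 allocated to each arm, the number X in the Mindlight arm is hypergeometric. The difference in institute share is (2X − K) / 60.

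| Institute share (assumed) | K | SD of difference | P(10 points or more) | P(15 points or more) | P(20 points or more) |
|---|---|---|---|---|---|
| 50% | 60 | 9.2 points | 0.36 | 0.10 | 0.04 |
| 60% | 72 | 9.0 points | 0.35 | 0.09 | 0.04 |
| 70% | 84 | 8.4 points | 0.32 | 0.07 | 0.03 |

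**What an imbalance does to the estimate.** Let g be the difference between contexts in change in anxiety, in SD units (assumed 0.2 to 0.8; the documents give no figure). The shift in the arm difference is the imbalance in share × g.

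- 10 points: 0.10 × 0.2 = 0.02 SD, up to 0.10 × 0.8 = 0.08 SD.
- 20 points: 0.20 × 0.2 = 0.04 SD, up to 0.20 × 0.8 = 0.16 SD.

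For two equal groups f = .25 corresponds to a difference of 2 × 0.25 = 0.5 SD, so the shift is small to moderate beside the planned effect.

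**Why g must be a difference in change.** The planned comparison concerns how anxiety develops over three time points. If children from institutes are simply more anxious throughout, that difference is constant within each child and drops out of the time-by-condition test. Only a context difference in change enters that test. The useful term is therefore context by time. A context main effect alone would not help.

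**What the trial could say by setting.** With a 50/50 split, a single time point and the normal approximation:

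- power within one setting for an effect of 0.5 SD is 0.49 with 120 children, and 0.41 with the 96 left after the plan's 20% loss (120 × 0.8);
- power to detect a 0.5 SD difference in effect between settings is 0.28 with 120 and 0.23 with 96.

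**The case against.** **TAU is already handled.** It is monitored, tested as a confounder and entered if unequal, and randomisation keeps the unadjusted comparison unbiased in expectation. This stands, and it is why the point is minor. It does not rescue the rule, because adjustment still depends on an observed imbalance and may use TAU measured after randomisation.

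**Provision is not receipt.** The sentence on TAU says who mainly offers it. A child recruited at a school may also attend an institute. This too stands, so context is a plausible correlate of TAU and no more. A reader might infer that it is a known predictor of outcome, but nothing in the article links either context or TAU to anxiety scores or to their change.

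**Allocation.** A reader might infer that allocation is not stratified by context. The article names no factor, but it is a condensed account and the full protocol may give one. The point about the model does not depend on this.

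**Variance explained.** It is tempting to argue that a 0.5-0.8 SD difference in level between contexts inflates the error term, and to express the loss as extra children needed. That does not apply to the time-by-condition test, from which a stable level difference drops out.

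**The two-setting conclusion.** A reader might want the implementation statement limited to settings whose own estimates support it. The trial recruits and delivers in both, so the pooled estimate is relevant to both. With power of 0.41-0.49 within a setting, such a limit would invite false negatives.

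**Conclusion.** The point holds as a minor improvement to a stated analysis rule. Recruitment context is fixed before allocation and plausibly related to background treatment, yet the rule omits it and relies on adjustment triggered by imbalance, partly on post-randomisation TAU. Prespecifying context is the better method.

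Under unstratified allocation with 50-70% of children from institutes, an imbalance of 10 points or more has probability 0.32-0.36 and would move the estimate by 0.02-0.08 SD. This rests on three assumptions: the split, unstratified allocation, and a context difference in change of 0.2-0.8 SD. If the contexts do not differ in change, the gain is small. If allocation is in fact stratified by context, the imbalance is largely removed, and the reason to include context is that the model should reflect the design.

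The documents do not show a biased primary comparison, an allocation that disregards context or an unsupported conclusion for either setting.

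**What to change.** - Enter recruitment context (institute or school) and its interaction with time as prespecified terms in the primary model and in the secondary models analysed the same way, whether or not the arms look balanced.
- State that imbalance-triggered adjustment for TAU measured after randomisation will not be relied on to handle differences between contexts. TAU by arm can still be monitored and reported.
- If allocation is stratified by context, say so and let the model reflect it.
- Estimates by setting may be reported descriptively with confidence intervals. The implementation statement should not be made to depend on them.

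The cost is one degree of freedom for context and, with three time points, (2 − 1) × (3 − 1) = 2 for its interaction with time. No new data are needed, since the source of recruitment is known for every child. The sample sizes of 86 and 120 do not change.

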### Sample size

A priori power analysis was performed in G*Power 3.1 [30] to calculate the sample size that is required in the present study. It is expected that Mindlight is significantly more effective in reducing anxiety symptoms of the participating children than Triple Town. Previous studies on the effect of already existing modified versions of CBT on anxiety among children with an ASD reported moderate to large effect sizes on anxiety symptoms (*e.g.* [31, 12, 32]). It is assumed that the implementation of Mindlight in clinical practice is worth consideration, when the effect of Mindlight is at least equal to the effect of the present anxiety treatments for children with an ASD. Therefore, the power calculation is conducted with a moderate expected effect size (f = .25) of condition (experimental or control condition) at 3-months follow-up. Moreover, it was expected that the Type I error was .05 and that the Type II error was .20 (power is .80). When computing these assumptions, it was calculated that a sample of 86 participants would be satisfactory in the present study. Eventually, the sample size was increased by 40 % to compensate for loss to follow-up (estimated at 20 %) and possible loss of power due to potential clustering of data in case of group formation (estimated at 20 %), resulting in 120 participants (60 in experimental condition and 60 in control condition).

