## Conclusion

This paper aimed to describe a study that will investigate the effect of the serious game Mindlight on (sub) clinical anxiety symptoms of children with an autism spectrum disorder in the age of 8–16 years old. It is expected that children in the experimental condition will show lower levels of anxiety symptoms at 3-months follow-up, compared to children in the control condition. If Mindlight turns out to be effective, this could provide a significant contribution to the evidence-based treatment of anxiety in children with an ASD.

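### The 86 participants do not follow from the stated effect at 3-month follow-up; the figure fits a test averaged over baseline, so the planned 80% power is not shown

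*Protocol article*

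**What the plan says.** The Sample size section names the software ("A priori power analysis was performed in G*Power 3.1") but not the procedure within it. It takes a "moderate expected effect size (f = .25) of condition (experimental or control condition) at 3-months follow-up". It sets the error rates by saying that "it was expected that the Type I error was .05" and that "the Type II error was .20 (power is .80"). From these assumptions it concludes that "it was calculated that a sample of 86 participants would be satisfactory in the present study". It then adds 40%, made up of 20% for loss to follow-up and 20% for possible clustering, "resulting in 120 participants (60 in experimental condition and 60 in control condition"). It gives no number of measurements and no correlation between them.

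The hypothesis concerns the same time point. The Conclusion expects that "children in the experimental condition will show lower levels of anxiety symptoms at 3-months follow-up" than controls, and the Discussion part of the Abstract says the same.

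The Data analysis section plans a 3 (time) by 2 (condition) repeated-measures ANOVA of child-reported anxiety. Its purpose is to compare how symptoms develop in the two groups, which is the time-by-condition interaction.

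**The concern.** The article prints an effect, an alpha, a power and a sample size that do not agree. The effect is stated as one "of condition (experimental or control condition) at 3-months follow-up", but the sample size belongs to a condition effect averaged over all three assessments.

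The difference matters because T0 precedes the intervention. In a randomised trial the true group difference at T0 is zero, so a difference of f = .25 at follow-up cannot also be a difference of f = .25 in the three-visit average unless T1 and T2 show much larger effects. The 80% therefore attaches neither to the follow-up hypothesis nor to the interaction that the analysis section sets out to test. Anyone who later interprets a null result would rely on a power figure that was not calculated for the question asked.

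**Working it through.** **Inputs from the article.** f = .25, alpha .05, power .80, two equal groups, three assessments, total N = 86 before inflation and 120 after, 20% loss to follow-up, 20% for clustering. For two equal groups f = d/2, so d = 0.5. **Assumptions added here:** equal variances and a common correlation rho between assessments. Power comes from the noncentral F distribution with noncentrality lambda.

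**1. Reproducing 86.** Between-groups test of a repeated-measures ANOVA with m = 3:

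lambda = f² × N × m / (1 + (m − 1) × rho), df 1 and N − 2.

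At rho = .5, lambda = 0.0625 × N × 3/2 = 0.09375 N. For N = 86, lambda = 8.06 and power is 0.801. For N = 84 power is 0.792. So 86 is the smallest even N that reaches 80%. Other values of rho give other sizes: 78 at .4, 96 at .6, 104 at .7. The inflation is consistent: 86 × 1.4 = 120.4.

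**2. The effect as stated, at follow-up alone.** Unadjusted comparison of two groups at T2: lambda = f² × N, df 1 and N − 2.

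- N = 86: lambda = 5.375, power 0.630
- N = 96 (120 × 0.8): lambda = 6.0, power 0.679
- N = 120: lambda = 7.5, power 0.775
- N = 128: lambda = 8.0, power 0.801, the first even N at or above 80%

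**3. The test behind 86, with a true baseline difference of zero.** For the averaged difference, lambda = (N/4) × (mean d)² / ((1 + 2 rho)/3). At rho = .5 the denominator is 2/3, and N = 86:

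- d = 0, 0.5, 0.5 at T0, T1, T2: mean d = 1/3, lambda = 86/24 = 3.58, power 0.465
- d = 0, 0, 0.5: mean d = 1/6, lambda = 86/96 = 0.90, power 0.155

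**4. The planned time-by-condition test.** lambda = (N/4) × Σ(d_t − mean d)² / (1 − rho), df 2 and 2(N − 2). For d = 0, 0.5, 0.5 the sum of squares is 1/9 + 1/36 + 1/36 = 1/6, so lambda = N / (24 (1 − rho)).

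| rho | N = 86 | N = 96 | N = 120 |
|---|---|---|---|
| .5 | 0.658 | 0.710 | 0.810 |
| .6 | 0.761 | 0.809 | 0.892 |
| .7 | 0.876 | 0.911 | 0.962 |

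The pattern 0, 0, 0.5 has the same sum of squares and so the same power. If the T1 effect is half as large (0, 0.25, 0.5), the sum is 1/8, and power at N = 96 is 0.58 for rho = .5 and 0.68 for rho = .6.

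**5. Baseline-adjusted comparison at T2.** lambda = f² × N / (1 − r²), df 1 and N − 3, where r is the T0–T2 correlation. At r = .5:

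- N = 96: lambda = 6.0/0.75 = 8.0, power 0.799
- N = 98: power 0.808
- N = 80: lambda = 5.0/0.75 = 6.67, power 0.722

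Here 80 is 96/1.2, which reads the 20% clustering allowance as a variance inflation of 1.2.

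**The case against.** The strongest reply is that 86 is not a slip. It comes out exactly from a standard procedure for a two-group, three-assessment repeated-measures ANOVA, which is the layout the trial plans to analyse. That stands, and the point is not that a sum was done badly. It does not rescue the figure, because the procedure tests the condition difference averaged over baseline as well, while both the sample-size text and the hypothesis speak of follow-up.

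A second reply is that no unadjusted single-visit comparison at T2 is planned, so 128 and 63% describe a test nobody will run. That also stands. A reader might infer that the trial has only 63% power, or that it must recruit more children. The documents support neither. The planned interaction test exceeds 80% with 96 evaluable children if rho is about .6 or higher. A baseline-adjusted T2 comparison would reach 80% even at 86 if r were about .58. Equally, the documents give no correlation on which to claim that power.

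A third reply is that clustering is only a contingency, since children are to play individually. So the figures for an effective 80 apply only if groups are formed.

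Finally, an article may leave the software procedure and the correlation to a fuller document. That is accepted: their absence alone would not be a finding. The finding is that the inputs printed do not yield the output printed.

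**Conclusion.** The stated inputs and the stated sample size contradict each other. For f = .25 at 3-month follow-up without adjustment, 128 are needed and 86 gives 63%. The 86 belongs to a test averaged over T0, T1 and T2 at an unstated correlation of .5. That test has 47% power at 86 if d = 0.5 holds at T1 and T2, and 16% if it holds at T2 only.

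For the time-by-condition test that the trial does plan, power with 96 evaluable children is 71% at rho = .5, 81% at .6 and 91% at .7. These figures assume a common correlation, d = 0.5 at follow-up and either the same effect or none at T1, and no clustering. They also treat the 20% lost as contributing nothing. They fall if the T1 effect lies between zero and 0.5. So 120 children may or may not be enough; what the article shows is that its 80% has not been established for its own question.

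**What to change.** Keep 120 and delete 86 as its basis. Then do one of the following.

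1. **Restate power for the time-by-condition test already planned.** Name the test, the effect assumed at each assessment and the correlation, and show a range: with 96 evaluable children, about 71% at rho = .5 and 81% at rho = .6, lower if clustering occurs. The cost is a reworded paragraph and, at the lower correlation, a less favourable stated power.

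2. **Name a baseline-adjusted contrast at T2 as the primary test,** which matches the follow-up hypothesis most directly. At r = .5 this has 79.9% power with 96 evaluable (98 are needed to pass 80%) and about 72% with an effective 80 if groups are formed. This changes the primary analysis in the Data analysis section, so it is an amendment and not just rewording, and it should be made before outcome data are examined.

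Neither option needs additional children.

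### Adding 20% for loss and 20% for clustering and applying 40% once to 86 does not cover both: if both occur, 120 randomised leaves an effective 77 to 83, not 86

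*Protocol article*

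**What the plan says.** All the figures are in the protocol article, under Sample size. The effect assumed is "a moderate expected effect size (f = .25) of condition (experimental or control condition) at 3-months follow-up". The error rates are given as "it was expected that the Type I error was .05" and "the Type II error was .20 (power is .80"). On these inputs "it was calculated that a sample of 86 participants would be satisfactory in the present study".

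The inflation follows: "Eventually, the sample size was increased by" 40%. The stated purpose is to make up for loss to follow-up, put at 20%, and for "possible loss of power due to potential clustering of data in case of group formation", also put at 20%, "resulting in 120 participants (60 in experimental condition and 60 in control condition"). No intracluster correlation, group size or design effect is given.

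The Data analysis/statistical analysis section names the primary model: "a 3 (within-subjects: pre, post, follow-up) by 2 (condition: experimental vs. control) ANOVA (repeated measures) will be conducted". The same section assumes that children play individually and that the data are not clustered. It provides a different analysis if groups form. The Procedure section also describes individual play in both arms.

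**The concern.** The 40% is the plain sum of two 20% allowances, applied once to the base number. This fails in two ways.

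- **Loss to follow-up.** If 20% of those randomised are lost, 80% remain. Keeping a target number therefore means dividing by 0.80, a factor of 1.25 and not 1.20.
- **Compounding.** Clustering reduces the information carried by the children who stay in the trial. It is a further factor on top of the first and cannot simply be added to it.

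The section says that the increase compensates for both losses. If it does not, the published justification for 120 is wrong in the one scenario for which the clustering allowance was added, and a reader would credit the trial with 80% power there when it has somewhat less.

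**Working it through.** **Inputs from the Sample size section:** f = 0.25, two groups, type I error 0.05, power 0.80, base number 86, loss 20%, clustering 20%, 120 randomised 1:1. **From the Data analysis/statistical analysis section:** three measurements. **Assumed:** a correlation of 0.5 between measurements, because the document gives none. It is used only for the power figures.

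**1. Reproduce the plan's figures.** For the between-group effect in a repeated-measures ANOVA, the noncentrality is N x f² x m / (1 + (m − 1) x rho). With m = 3 and rho = 0.5 this is N x 0.0625 x 3 / 2 = 0.09375 N. At N = 86 it is 8.06, and the F test on 1 and 84 degrees of freedom has power 0.801. N = 86 is the smallest even number that reaches 0.80. The inflation is 86 x 1.40 = 120.4, stated as 120. Both figures reproduce, so the percentages were summed.

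**2. Apply both allowances to 120.** The text does not say what the 20% for clustering means, so three readings are shown. Power uses the test in step 1.

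| Reading | Effective N from 120 | Power | Needed for 86 effective |
|---|---|---|---|
| Both as a factor of 1.2 (most lenient) | 120 / 1.44 = 83.3 | 78.9% | 86 x 1.44 = 123.8, so 124 |
| 20% lost, design effect 1.2 | 120 x 0.80 / 1.20 = 80 | 77.2% | 86 x 1.20 / 0.80 = 129 (130 for equal arms) |
| 20% lost, then 20% of effective N lost | 120 x 0.80 x 0.80 = 76.8 | 75.5% | 86 / 0.64 = 134.4, so 135 (136 for equal arms) |

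Every reading falls below 86. Even the most lenient needs a factor of 1.44, against the 1.40 applied.

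**3. Loss without clustering.** 86 / 0.80 = 107.5, so 108 randomised would be enough. With 120 randomised, 120 x 0.80 = 96 complete, and power is 84.4%.

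**4. What 120 can absorb while keeping 86 effective.**
- With 20% loss: a design effect up to 96 / 86 = 1.116, about 1.12.
- With a design effect of 1.2: loss up to 1 − (86 x 1.2) / 120 = 0.14, or 14%.
- With no clustering: loss up to 1 − 86 / 120 = 0.283, or 28%.

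**The case against.** The strongest reply is that the plan does not expect clustering. Individual play is the design, the unclustered analysis is the default, and the clustering loss is called possible. In that base case 120 leaves 96 completers, ten more than the target. This stands, and it makes the shortfall conditional. It does not rescue the sentence, which claims compensation for both losses and gives a number that does not provide it.

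A second reply is that the text fixes no design effect, so neither 80 nor 129 is determined. That also stands, and for that reason a range is given. The direction is the same across the range.

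A third is that all randomised children are analysed, with multiple imputation for missing outcomes. Imputation keeps the children in the analysis but does not in general restore the information lost with their outcomes. The plan itself treats loss as needing compensation.

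A reader might also infer more than the document supports:
- *That the trial fails to deliver 80% power.* It does so only if both losses occur at about the sizes named.
- *That 80% holds only if no groups form.* This is false. Groups can form and 86 effective can remain, within the limits in step 4 of the working.
- *That this error accounts for any mismatch between 86 and an effect located at the 3-month follow-up.* How the base number was obtained is a separate matter. The inflation fault is there whatever the base.

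**Conclusion.** Wrong as written, and modest in size. The inflation to 120 does not compensate for the two losses it names. If both occur, the effective sample is about 80 (76.8 to 83.3), and 120 is about 9 children short of what full compensation needs (4 to 16 across the readings, the upper end for equal arms). Power falls from 80% to about 77% (75% to 79%).

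The sample-size shortfall follows from the section's own percentages and needs no outside input beyond the reading of the clustering figure. The power figures rest on the test that reproduces 86 and on the assumed correlation of 0.5. If children play individually, as planned, 120 is more than enough for the stated loss.

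**What to change.** Keep 120 and correct the sentence in the Sample size section. It should say that:

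- 120 randomised covers a 20% loss to follow-up alone, with about 84% power;
- with 20% loss and a 20% clustering loss together, power is about 77% (75% to 79% by how the clustering figure is read);
- with 20% loss, 80% power is kept only up to a design effect of about 1.12.

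It should also state the correlation between measurements that was used, since these power figures depend on it, and whether the clustering 20% is a design effect or a loss of effective sample.

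The cost is a rewritten sentence or two and a less favourable power figure for the clustered case. No extra children are needed, and neither design nor analysis changes. Only if the sponsor wants both losses fully covered would the target rise, to about 129 (130 for equal arms) on the design-effect reading.
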